### 5.5. Missing data (optional)

We will use multiple imputation to handle missing data. This statistical technique is a relatively flexible, general purpose approach to dealing with missing data [103].

### 5.6. Exploratory analysis (optional)

We will explore the relationships between our dependent variables (external acceptance, personal acceptance, depression, anxiety, stress and camouflaging) and various individual differences (e.g., autistic traits, alexithymic traits, gender, level of education, age of diagnosis, income etc.). For continuous variables, we will run simple (Bonferroni-corrected) correlations between our dependent variables and demographic factors (e.g., age, autistic traits). For categorical variables, we will use Bonferroni-corrected independent samples t-tests to compare levels of autism acceptance, camouflaging and mental health difficulties across the demographic factor (e.g., gender). For example, as gender is a categorical variable, we will use Bonferroni-corrected independent samples t-tests to compare levels of acceptance, camouflaging and mental health across genders. Conducting these analyses will allow us to verify whether any individual differences are associated with any of our dependent variables as has been found previously in some instances (e.g., camouflaging and gender; [41]).

Then, we will conduct our MANOVA again whilst controlling for any of the individual differences that are associated with our dependent variables or which differ significantly between groups. This will allow us to determine whether there are cultural differences in autism acceptance, camouflaging and mental health that go beyond these specific individual differences.

Moreover, in order to investigate whether camouflaging mediates any relationships we identify between autism acceptance and mental health outcomes, we will complete mediation analyses. There are several methods used to test the statistical significance of mediated effects [104–106]. In the present study, we will use structural equation modelling (SEM), a powerful statistical technique used to infer causal relationships between variables, for our mediation analyses. We decided to use SEM over standard regression methods (as outlined by Baron and Kenny; [107]) as this technique is regarded as “a more appropriate inference framework for mediation analyses” (see [108]). In addition, we will use bias-corrected bootstrapping to create confidence intervals as there is a consensus that it is the most powerful method for testing mediated effects [104, 109–112]. Whilst we believe that there will be sufficient statistical power to detect an effect, we may supplement this analysis with Bayesian mediation analyses if it appears that we are underpowered.

In addition, we will calculate standardised residuals for the relationships between autism acceptance and mental health, autism acceptance and camouflaging, and camouflaging and mental health, for all participants. Then we will complete an exploratory MANOVAs in which we will compare the standardised residuals across countries. This will allow us to compare the strength of these relationships in each of the countries by comparing the levels of unexplained variance following regression analyses. This is useful because the strengths of these relationships could, in principle, vary across our countries. For example, it could be that in collectivist, relative to individualistic, cultures, camouflaging accounts for a smaller portion of variance in mental health as hiding any traits that deviate from the norm is common (and therefore may not be detrimental to mental health).

Finally, in order to compare the strength of the relationships between our dependent variables across genders, we will complete an additional exploratory MANOVA using the standardised residuals discussed above. This is useful because the strength of the relationships between our dependent variables could vary across genders: it could be the case, for instance, that there is a stronger relationship between autism acceptance and camouflaging in autistic women than autistic men, thus explaining the higher rates of camouflaging displayed by autistic women [40–48]. In addition, it could be that there is a weaker relationship between camouflaging and mental health difficulties in autistic men since they more frequently report positive consequences of camouflaging [38].

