### 3.3. Sample size (required)

The final sample in this study will comprise at least 286 autistic adults (aged over 18) from across the globe.

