**Fig 1 pone.0261774.g001:**
[figure not shown]
A diagram showing the relationships that we will test in the current study. The plus (+) indicates a positive relationship between the variables and the minus (-) indicates a negative relationship.

Please note that for the following sample size calculations, we used an Bonferroni-adjusted alpha level of 0.0125 to account for multiple testing (4 regression analyses), and a power level of 90% (thereby giving us higher power than is standard in the field [85, 86]). To replicate the finding from Cage et al., that external acceptance and personal acceptance account for 17.5% variance explained in depression scores after controlling for age, gender, age of diagnosis, anxiety and stress (f^2^ = 0.37), 51 participants are required. In order to replicate the finding that external acceptance and personal acceptance account for 3% variance explained in stress scores after controlling for age, gender, age of diagnosis, anxiety and stress, 246 participants are required. To replicate the finding from Perry et al., that stigma significantly predicts camouflaging (f^2^ = 0.069) after controlling for age, gender, age of diagnosis, and autistic traits, 211 participants are required. Finally, in order to replicate the finding that anxiety accounts for 4% variance explained in camouflaging scores after controlling for age and autistic traits, 286 participants are required. Therefore, the final sample will comprise at least 286 participants (with full datasets).

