#### 3.4.2. Comparing autism acceptance, camouflaging and mental health across cultures

In the analyses where we will compare participants’ experiences of autism acceptance, camouflaging, and levels of depression, anxiety and stress across countries, we will only include data from countries that have at least 30 participants (and therefore we will have sufficient data to draw comparisons between these multiple groups). We selected this cut-off as Sekaran [87] highlights that “where samples are to be broken into sub-samples…a minimum sample size of 30 for each category is necessary”. Importantly, Sekaran [87] also highlights that “in multivariate research…the sample size should be several times (preferably 10 times or more) as large as the number of variables in this study”. By recruiting at least 286 participants to our study, our sample is over 47 times larger than the number of variables in our multivariate analysis (6 variables: external acceptance, personal acceptance, camouflaging, depression, anxiety and stress), is as large as necessary based on our power analyses (largest sample size generated = 286), and would facilitate comparisons between participants in up to 9 countries.

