### 5.3. Inference criteria (optional)

For our regression analyses, to account for the four tests we will use a p < .0125 significance threshold to determine whether to accept or reject the null hypothesis. For our MANOVA, we will use a p = .05 significance threshold.

In our analyses, Bayes Factors (BF_01_) may be reported, which provide a ratio of the likelihood for the observed data under the null hypothesis compared to the alternative hypothesis [101]. For all Bayesian analyses, we will follow the classification scheme in JASP outlined by Lee and Wagenmakers [102]: BF_10_ values between one and three will be considered as weak evidence, between three and ten as moderate evidence and greater than ten as strong evidence for the alternative hypothesis.

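### Covariates for the adjusted country MANOVA are chosen by significance from an open list, which can drop weak confounders; naming them in advance is a cheap, modest improvement

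*Protocol article*

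**What the plan says.** Section 5.6 (Exploratory analysis) first relates the six dependent variables to an open-ended set of individual differences. Autistic traits, alexithymic traits, gender, education, age of diagnosis and income are given as examples. Continuous candidates are screened by Bonferroni-corrected correlations. "For categorical variables, we will use Bonferroni-corrected independent samples t-tests" are prescribed for the rest, with gender as the example.

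The MANOVA is then rerun "controlling for any of the individual differences that are associated with our dependent variables or which differ significantly between groups". The stated purpose is to "determine whether there are cultural differences in autism acceptance, camouflaging and mental health that go beyond these specific individual differences".

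Three other places bear on this:

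- Section 5.1.2: the confirmatory MANOVA has country as its only factor and no covariates. Section 5.3 sets its level: "For our MANOVA, we will use a p = .05 significance threshold".
- Section 4.2.5: the AQ and TAS-20 are included partly so that analyses can control for them, with a pointer to the exploratory analyses.
- Section 5.1.1: the four regressions use covariates fixed in advance.

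**The concern.** Whether a characteristic is adjusted for depends on significance tests in the same data. A candidate that fails both screens is left out, although failing to reach significance is not evidence that it does no confounding. Correcting the outcome screen for many tests makes such failures more common.

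Sample composition may well differ by country. Section 3.2 recruits through network sites in Belgium, Japan, the UK and the USA, through Prolific for Australia, Canada and South Africa, and through social media. The rerun in Section 5.6 is the plan's only covariate-adjusted test of mean country differences, so whatever the screen drops stays mixed into the country effect.

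The rule is also not fully reproducible: the candidate list is open, the number of Bonferroni tests is not stated, and the level for the between-group screen is not given. It makes control for AQ and TAS-20 conditional, although Section 4.2.5 says they are collected for that purpose.

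**Working it through.** **Inputs from the document.** Sample size: "The final sample in this study will comprise at least 286 autistic adults (aged over 18) from across the globe". Dependent variables: "6 variables: external acceptance, personal acceptance, camouflaging, depression, anxiety and stress". Seven countries are named in Section 1.1.3; 286/7 is about 41 per country, above the minimum of 30 in Section 3.4.2.

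**Assumptions not in the document.** Number of Bonferroni tests m = 36 (6 outcomes x 6 named candidates) to 60 (6 x 10). Country screen at 0.05, or at 0.005 if it too is corrected for ten candidates. Seven equal countries with evenly spaced covariate means. One confounder, linked to one outcome.

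**The plan's own figure.** Section 5.6 prints no number, so the only figure to reproduce is the 286 behind it. Section 3.4.1 states that "anxiety accounts for 4% variance explained in camouflaging scores after controlling for age and autistic traits, 286 participants are required". At alpha 0.0125 and 90% power, 286 needs f² = 0.0505, that is, 0.04/(1 - R²) with a full-model R² of about 0.21. That R² is not printed, so 286 can be neither confirmed nor faulted. It is taken as given here.

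**Step 1, outcome screen alone.** Power is approximately Φ(atanh(r)·√(n - 3) - z), with √283 = 16.82. The two-sided critical value z is 3.197 for 0.05/36 and 3.341 for 0.05/60. For r = 0.15, atanh(r)·√283 = 2.543, giving Φ(-0.65) = 26% and Φ(-0.80) = 21%.

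| r | m = 36 | m = 60 |
|---|---|---|
| 0.10 | 7% | 5% |
| 0.15 | 26% | 21% |
| 0.20 | 59% | 53% |
| 0.25 | 86% | 83% |
| 0.30 | 98% | 97% |

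**Step 2, country screen alone.** One-way ANOVA F test with noncentrality f²·286:

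| f | level 0.05 | level 0.005 |
|---|---|---|
| 0.10 | 19% | 4% |
| 0.15 | 42% | 15% |
| 0.20 | 70% | 38% |

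**Step 3, the full either-or rule.** Share of samples in which the confounder is omitted, by simulation (600 repetitions per cell; ranges cover m = 36 to 60):

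| r, f | country screen 0.05 | country screen 0.005 |
|---|---|---|
| 0.10, 0.10 | 73-78% | 89-91% |
| 0.15, 0.10 | 60-65% | 70-75% |
| 0.15, 0.15 | 43-47% | 64-69% |
| 0.20, 0.20 | 14-16% | 23-30% |
| 0.30 | at most 3% | at most 4% |

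A hand check treats the two screens as independent. For r = 0.15, f = 0.15, m = 36 and level 0.05, (1 - 0.256)(1 - 0.422) = 0.43, in line with the simulation.

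**Step 4, size of the bias.** With seven evenly spaced means, the extreme countries differ by 3f within-country SDs of the covariate. The bias in the outcome gap is therefore about 3·r·f/√(1 + f²). For r = f = 0.10 this is 0.03 SD; for r = 0.15, f = 0.20 it is 0.09 SD.

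**Step 5, false positives with no true country effect.** With one confounder (univariate country test, m = 60, 2,500 repetitions), the rate is 0.042-0.058 under the plan's rule and 0.042-0.057 when always adjusting; the largest difference in any cell is 0.002. With four to six weak confounders all tilted the same way across countries, it rises to at most about 0.08-0.10 with the country screen at 0.005, and to 0.05-0.06 with it at 0.05. With a fixed list it stays at about 0.05.

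**The case against.** The strongest reply is that the rule has two routes, and a confounder of the country comparison must differ between countries, which the second route targets directly. This stands. It would be wrong to infer that every covariate must pass a Bonferroni-corrected test, because the correction is stated only for the outcome screen.

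A reader might also infer that real confounders will usually be missed. Step 3 does not support that: omission exceeds about half only when r is 0.15 or less and the country imbalance is small. Linking the covariate to several outcomes helps further. With 72 tests and three outcomes intercorrelated at 0.5, the outcome route alone retains about 38%, 76% and 95% at r = 0.15, 0.20 and 0.25.

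Nor does the data-driven choice make the adjusted p-value meaningless. For one confounder Step 5 shows practically no distortion.

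The plan does not overclaim as strongly as a partial reading suggests. Its purpose statement is restricted to the particular characteristics adjusted for, and the section is labelled exploratory.

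On the t-tests, the plural wording can be read as corrected pairwise comparisons, which would be acceptable for a factor with several levels. What remains is a need for clarity, since Section 4.2.1 collects gender identity, ethnicities and education, each of which may have more than two categories.

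What survives is narrower: a significance screen is an unreliable guide for weak confounders, and nothing is gained by relying on it when the candidates are known and measured.

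**Conclusion.** The point holds as a modest improvement to an exploratory analysis. Under the stated assumptions, a weak confounder (r = 0.15, f = 0.10-0.15) is omitted in about 43-75% of samples, while one at r = 0.20, f = 0.20 is kept in about 70-86% and one at r = 0.30 in at least 96%. Each omission of a weak confounder costs about 0.03-0.09 SD in the extreme country gap; the practical risk comes from several acting together.

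These figures depend on the number of tests, the country-screen level and equal groups, none of which the document fixes. A sample above the 286 minimum would make the screen more sensitive, and dropping countries with fewer than 30 participants would reduce the number available. The document does not support the stronger conclusion that the confirmatory MANOVA of Section 5.1.2 is invalid: it does not use this rule.

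**What to change.** In Section 5.6, replace the selection rule with two adjusted MANOVAs named in advance and reported whatever the screening shows:

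- Model 1: country plus age, gender, age of diagnosis, level of education and income.
- Model 2: Model 1 plus AQ and TAS-20.

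Keep the correlations and group comparisons as description only. State that any conclusion about country differences beyond individual differences refers to the covariates in the model. For characteristics with more than two levels, specify a one-way ANOVA or regression F test.

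All these variables are already collected under Section 4.2. The cost is revised wording and a few degrees of freedom out of at least 286 participants.

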However, a burgeoning literature suggests that camouflaging may be a risk factor for depression and anxiety in autism [25, 37, 53–57], irrespective of gender [58]. Interestingly, Cage and colleagues [37] suggest that camouflaging may mediate the relationship between social stressors (e.g., lack of autism acceptance, bullying) and anxiety and depression. That is, those who experience more social stressors (such as a lack of autism acceptance) are more likely to camouflage their autistic traits, which in turn results in higher levels of anxiety and depression. However, a recent study found that whilst autism-related stigma was associated with lower wellbeing, camouflaging did not mediate this relationship (despite camouflaging being positively associated with autism-related stigma; [59]). Future research should verify whether camouflaging mediates the relationship between autism acceptance/stigma and anxiety and depression more specifically.

It is important to note that the terms we use to refer to camouflaging vary across the globe [60]. In Japan, the term ‘over-adaptation’ is used to describe excessive efforts made by people (i.e., society more broadly) to meet external demands and expectations, even if this means forcibly suppressing their internal needs [61]. In recent years, this term has been applied to autism to describe the substantial efforts made by autistic people to fit into an environment as a result of differences in interpersonal and social behaviour [62–64]. As such, this concept is highly similar to the construct of camouflaging (see [61] for a discussion around the similarities and differences between the constructs of camouflaging and over-adaptation in autism). Importantly, there is anecdotal evidence that over-adapatation is associated with poorer mental health in autistic individuals in Japan [65]. However, to date no empirical studies have tested this relationship [61], and therefore further study of over-adaptation and camouflaging in Japan is necessary.

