### 5.1. Statistical models (required)

First, in our regression analyses, we will include data for all participants that completed the study in one group (collapsing across countries) to explore relationships in a large and cross-cultural sample of autistic adults. For these four regression analyses, we will use a p < .0125 threshold to establish whether to reject the null hypothesis (corrected for multiple testing). Then, we will separate participants into groups based on their country of residence and compare participants’ experiences of autism acceptance, camouflaging, and levels of depression, anxiety and stress across these groups.

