#### 5.1.1. Replicating the regression analyses from previous research

Following the procedures from Cage et al., [37], we will complete two hierarchical regression analyses with depression and stress as the outcome variables respectively. Blockwise entry will be used to analyse the data: in step one, age, age of diagnosis, gender and the other DASS subscale scores will be entered. In the second step, the two types of acceptance (external sources and personal) will be added.

In line with the procedures outlined in Perry et al., [59], we will complete a multiple regression analysis with camouflaging as the dependent variable, and autism acceptance, age, gender, age of diagnosis and autistic tratis as the independent variables.

As in Hull et al., [58], we will complete a hierarchical regression analysis with anxiety as the dependent variable. In step one, age and autistic traits will be added into the model. In step two, camouflaging will be entered into the model.

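### Mediation is limited to acceptance–outcome relationships already identified, which leaves the acceptance–camouflaging–anxiety path without a planned route into the analysis

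*Protocol article*

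**What the plan says.** Section 5.6 of the protocol article introduces the mediation analyses "in order to investigate whether camouflaging mediates any relationships we identify between autism acceptance and mental health outcomes". It does not define what counts as having identified a relationship. On method it states: "We decided to use SEM over standard regression methods". The method set aside is the causal-steps approach. Intervals are to come from bias-corrected bootstrapping, chosen for its power.

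The models that could identify an acceptance–outcome relationship are in section 5.1.1: "we will complete two hierarchical regression analyses with depression and stress as the outcome variables respectively". Acceptance enters both of these at step two. A third model regresses camouflaging on acceptance. The fourth has anxiety as its outcome, with age and autistic traits at step one and camouflaging at step two. Acceptance is not in it. Section 5.1 sets the threshold: "For these four regression analyses, we will use a p < .0125 threshold to establish whether to reject the null hypothesis".

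Section 1.1.1 gives the motivation: "Future research should verify whether camouflaging mediates the relationship between autism acceptance/stigma and anxiety and depression more specifically".

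**The concern.** Two features combine.

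- **The condition comes first.** Requiring a detected total effect before examining an indirect effect is the opening step of the causal-steps approach that section 5.6 says it is replacing. With no direct effect, the total effect is the product of two links, so its test can be far weaker than the test of the indirect effect placed behind it.
- **Anxiety has no entry test.** Acceptance to camouflaging and camouflaging to anxiety are both planned regressions with sample-size calculations. This is the only acceptance–camouflaging–outcome chain whose two links are both in the confirmatory set. No planned regression or hypothesis relates acceptance to anxiety, so no stated step would identify that relationship.

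The risk is that the study leaves one of its own motivating questions unanswered, or answers it only after an unplanned association turns up and the path is selected on significance.

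**Working it through.** **Inputs**

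- n = 286, the planned minimum (section 3.4.1).
- Link a, acceptance to camouflaging: f² = 0.069 (section 3.4.1). The source predictor is stigma, so the sign is reversed for acceptance.
- Link b, camouflaging to anxiety: 4% of variance (section 3.4.1). The sentence there is worded as anxiety explaining camouflaging. b = √0.04 = 0.20 is an assumption.
- Entry threshold: .0125 (section 5.1), with .05 as the lenient alternative.
- Standardised paths, one acceptance predictor, no covariates.

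**Reproducing the plan's figures.** Noncentral F test for an R² increase, λ = f²·n, alpha .0125, power 90%. One tested predictor with f² = 0.069 gives n = 211, as stated. Two tested of seven predictors with f² = 0.37 gives n = 51, as stated. The figure of 286 does not follow from 4% alone (f² = 0.04/0.96 gives 346), so it is used here only as the sample size.

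**Anxiety path, no direct effect (c′ = 0)**

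1. a = -√(0.069/1.069) = -0.254.
2. Total effect = a·b = -0.254 × 0.20 = -0.051.
3. f² for the total effect = 0.0508²/(1 - 0.0508²) = 0.0026.
4. Probability that the total effect is significant at n = 286: 14% at .05 and 5% at .0125 by noncentral F; about 13% and 4–5% by simulation.
5. Indirect effect, using joint significance of a and b as a stand-in for the bootstrap. Power for a at .05 is 0.993. For b given acceptance, f² = 0.04(1 - 0.0645)/0.96 = 0.039, with power 0.914. Product: 0.993 × 0.914 = 0.91. A bootstrap simulation gave 91–93%.
6. Both conditions met (simulation): about 12% with entry at .05, and about 4% at .0125.
7. Indirect effect at .05/6 = .0083: 0.962 × 0.752 = 0.72 by noncentral F, about 71% by simulation.

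**Sensitivity (n = 286; indirect effect judged at .05)**

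| a | b | c′ | Found with entry at .0125 / .05 | Found with no entry condition |
|---|---|---|---|---|
| -0.254 | 0.20 | 0 | 4% / 12% | 91% |
| -0.254 | 0.30 | 0 | 12% / 25% | 99% |
| -0.254 | 0.20 | -0.10 | 47% / 66% | 91% |
| -0.254 | 0.20 | -0.20 | 89% / 91% | 92% |
| -0.50 | 0.50 | 0 | 97% / 99% | 100% |

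**Depression and stress.** For depression, f² = 0.37 with two tested of seven predictors gives power above 99.9% at n = 286 and .0125, so the condition is met almost surely. For stress, the f² implied by the stated n of 246 (about 0.07) gives about 95%. Reading the 3% literally (0.03/0.97 = 0.031) gives 56% at .0125 and 76% at .05.

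**The case against.** The strongest reply is that the condition does little harm where the plan gives an acceptance–outcome effect. Depression, one of the two outcomes named in section 1.1.1, passes almost surely, and stress passes in 56–95% of studies depending on how the 3% is read. This stands. A reader might infer that the mediation question as a whole is mostly lost, or that complete mediation will generally be missed. The documents do not support that. The planned 17.5% for depression could not arise by complete mediation through a link of 0.254, since b would have to be about √0.175/0.254 = 1.65. With large links the loss nearly disappears.

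Second, the word 'identify' is not tied to a p-value. Section 5.3 allows Bayes factors, and section 5.6 speaks of mental health outcomes generally and plans residuals for acceptance and mental health. So the anxiety path is not excluded, and it would go too far to say it will never be tested. But the residuals serve comparisons between countries and genders, and none of this sets a test of acceptance against anxiety. The looser reading leaves the choice of mediation models until the data have been seen.

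Third, the analysis is declared exploratory, and asking whether a mediator explains an observed association is a legitimate question. That stands and lowers the stakes. It does not explain why a path named as an open question should depend on a test the plan does not contain.

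Fourth, a correction over six tests is not a trivial cost. This also stands: power for the anxiety path drops from about 91% to about 71%.

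**Conclusion.** The point holds for anxiety. The acceptance–camouflaging–anxiety path has no planned route into the mediation analysis. If entry requires a significant total effect, then with no direct effect the chance of finding mediation on this path falls from about 91% to about 12% (entry at .05) or 4% (entry at .0125). Even against a Bonferroni-corrected test at about 71%, the gap is wide. It narrows to 66% against 91% with a direct effect of -0.10 and almost closes at -0.20.

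These figures are a scenario: the documents give no acceptance–anxiety effect, b is taken as the square root of a variance increment, a comes from a stigma predictor, and covariates are ignored. No confirmatory conclusion is affected. The change is worth making because it is cheap and lets the study answer a question it raises itself.

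**What to change.** In section 5.6, replace the conditional phrase with a fixed list: external and personal acceptance, each with depression, anxiety and stress as outcome and camouflaging as mediator. Estimate all six indirect effects whatever the total effect, and report all of them with intervals, labelled exploratory.

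State whether a multiplicity correction applies. If Bonferroni over six is used, say that power for the anxiety path is roughly 71% under the assumptions above; Holm would be no lower. If none is used, say that the intervals are uncorrected.

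The cost is one rewritten sentence and a few more model outputs, with no new data. The only statistical price is the power given up if a correction is chosen.
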